## Abstract

**Background:**

The position of arterial ligation during laparoscopic anterior rectal resection with total mesorectal excision can affect genito-urinary function, bowel function, oncological outcomes, and the incidence of anastomotic leakage. Ligation to the inferior mesenteric artery at the origin or preservation of the left colic artery are both widely performed in rectal surgery. The aim of this study is to compare the incidence of genito-urinary dysfunction, anastomotic leak and oncological outcomes in laparoscopic anterior rectal resection with total mesorectal excision with high or low ligation of the inferior mesenteric artery in a controlled randomized trial.

**Methods/design:**

The HIGHLOW study is a multicenter randomized controlled trial in which patients are randomly assigned to high or low inferior mesenteric artery ligation during laparoscopic anterior rectal resection with total mesorectal excision for rectal cancer. Inclusion criteria are middle or low rectal cancer (0 to 12 cm from the anal verge), an American Society of Anesthesiologists score of I, II, or III, and a body mass index lower than 30. The primary end-point measure is the incidence of post-operative genito-urinary dysfunction. The secondary end-point measure is the incidence of anastomotic leakage in the two groups. A total of 200 patients (100 per arm) will reliably have 84.45 power in estimating a 20% difference in the incidence of genito-urinary dysfunctions. With a group size of 100 patients per arm it is possible to find a significant difference (α = 0.05, β = 0.1555). Allowing for an estimated dropout rate of 5%, the required sample size is 212 patients.

**Discussion:**

The HIGHLOW trial is a randomized multicenter controlled trial that will provide evidence on the merits of the level of arterial ligation during laparoscopic anterior rectal resection with total mesorectal excision in terms of better preserved post-operative genito-urinary function.

**Trial registration:**

ClinicalTrials.gov Identifier: NCT02153801

Protocol Registration Receipt 29/5/2014.

**Electronic supplementary material:**

The online version of this article (doi:10.1186/s13063-014-0537-5) contains supplementary material, which is available to authorized users.

## Background

Colorectal cancer incidence and mortality rates vary around the world. Globally, colorectal cancer is the third most commonly diagnosed cancer in men and the second in women [1]. Surgical treatment of rectal cancer has changed radically in recent years. The introduction of total mesorectal excision [2], neo-adjuvant therapy protocols [3], and the laparoscopic approach [4] has made rectal cancer treatment a multidisciplinary management.

While laparoscopic resection of colon cancer has slowly gained acceptance worldwide, the role of laparoscopy in the treatment of rectal cancer is still controversial [4,5]. The laparoscopic treatment of rectal cancer raises specific issues related to its anatomical location: difficult exposure in a narrow pelvis, challenging nerve-sparing techniques, low intestinal transection, and total mesorectal excision [6,7]. Ligation of the inferior mesenteric artery at the origin and mobilization of the splenic flexure are not routinely done worldwide [8-11]. The need for well-designed studies to compare the different vascular approaches in rectal surgery has been clearly expressed [12-14].

The level of arterial ligation can affect genito-urinary function (injury to the superior hypogastric plexus), the extent (and yield) of lymphadenectomy, and distal colonic arterial perfusion (especially in older people, where distal colonic arterial perfusion could be deficient due to degenerative disease), and causesympathetic nerve injures [15-19]. Moreover, colonic stump blood supply and anastomosis tension are the main factors in developing leaks in rectal surgery [20-26] and are dependent on the level of ligation.

The aim of this study is to compare the incidence of genito-urinary dysfunction and, secondarily, the incidence of anastomotic leakage and the oncological outcomes in laparoscopic anterior rectal resection with total mesorectal excision with high or low ligation of the inferior mesenteric artery in a controlled randomized trial.

## Methods/design

### Study design

The HIGHLOW study is a multicenter controlled trial. Patients are randomly assigned to high or low inferior mesenteric artery during laparoscopy once the surgeon has confirmed intraoperatively, that all inclusion criteria are fulfilled and that the procedure is feasible. All participating surgeons have performed at least 20 laparoscopic procedures per year during the past 5 years. Randomization is performed using sealed envelopes (Figure 1).

**Figure 1 Fig1:**
[figure not shown]
**Study flowchart.** LAR: Laparoscopic Anterior Resection. TME: Total Mesorectal Excision.

### Primary and secondary endpoint measures

The primary end-point measure is the incidence of post-operative genito-urinary dysfunction compared with a preoperative base-line assessment in both groups. The secondary endpoint measures are the incidence of clinical or subclinical anastomotic leakage in the two groups and the oncological outcomes in both groups.

The incidence of clinical or subclinical anastomotic leaks will be determined either as the presence of a radiologically, endoscopically, or surgically proved fistula or as the presence of a subclinical leak observed by endoscopic examination 30 days after surgery in both groups.

Oncological outcomes will be assessed in terms of retrieved lymph nodes, number of positive lymph nodes on the root of the inferior mesenteric artery total number of lymph nodes of the mesorectum, and positive lymph nodes of the mesorectum, disease-free survival, overall survival, local recurrence, distant metastasis in both groups.

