### Study population

The study population consists of patients with cancer of the lower two-thirds of the rectum, who are eligible for laparoscopic low rectal resection with total mesorectal excision.

Inclusion criteria are middle or low rectal cancer (from 0 to 12 cm from the dental line), an American Society of Anesthesiologists score of I, II, or III, and a body mass index less than 30. The study will include both preoperatively irradiated and non-irradiated patients.

Exclusion criteria are prior surgery on the abdominal aorta and proven arteriosclerosis of the inferior mesenteric artery and its branches.

The study will include both pre operatively irradiated and non-irradiated patients.

Exclusion criteria: prior surgery on the abdominal aorta, proven arterosclerosis of IMA and IMA branches.

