### Preoperative evaluation

Patients with a preoperative diagnosis of adenocarcinoma of the middle or lower rectum and who satisfy the inclusion criteria will be asked to participate in the HIGHLOW trial. Once informed consent is obtained, investigations will include questionnaires for the International Index of Erectile Function [27], International Consultation on Incontinence Questionnaire [28], International Prostatic Symptoms Score, Female Sexual Function Inde [29] Uroflowmetry and ultrasound measurement of post-void bladder volume will be performed pre-operatively for all patients.

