### Sample size calculation

A two tail Fischer exact test applied to two cohorts of 100 patients each will have 84.45 power in estimating a 20% difference in the incidence of genitor-urinary dysfunctions. With a group size of 100 patients per arm it is possible to find a significant difference (α= 0.05, β= 0.1555).

With a drop-out estimated rate of 5%, the required sample size is 212 patients. If the number of drop-outs exceed 5%, we plan to ask the ethics committee to enroll more patients to be able to keep the power of analysis well above 80%.

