### Statistical analysis

The Primary end-point measure will be evaluated using Fisher’s exact test (one-sided). The different incidences of genitor-urinary dysfunction according to sex and the results of each questionnaire will be evaluated using the Mann–Whitney *U test* and the *t-*test. Mc Nemar’s test will be used to evaluate changes in questionnaires results overtime. Statistical analysis will be performed in accordance with the intention-to-treat principle.

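### The primary between-arm test is an unadjusted Fisher test although baseline function is measured and the endpoint is framed against it: valid, but it gives up power and precision

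*Protocol article*

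**What the plan says.** - **Endpoint** (Primary and secondary endpoint measures), defined as follows: "The primary end-point measure is the incidence of post-operative genito-urinary dysfunction compared with a preoperative base-line assessment in both groups". Nothing in the text says whether a case is any dysfunction after surgery, new-onset dysfunction, or worsening from baseline.
- **Baseline data** (Preoperative evaluation): four questionnaires on erectile function, incontinence, prostatic symptoms and female sexual function; also "Uroflowmetry and ultrasound measurement of post-void bladder volume will be performed pre-operatively for all patients".
- **Primary test** (Statistical analysis), named as follows: "The Primary end-point measure will be evaluated using Fisher’s exact test (one-sided". No covariate or stratification is named.
- **Eligibility** (Study population): the exclusions concern aortic surgery and arteriosclerosis of the artery and its branches. Patients with existing genito-urinary dysfunction may enter. On radiotherapy, "The study will include both preoperatively irradiated and non-irradiated patients".
- **Sizing** (Sample size calculation), justified as follows: "A two tail Fischer exact test applied to two cohorts of 100 patients each will have 84.45 power in estimating a 20% difference". Losses are then allowed for: "With a drop-out estimated rate of 5%, the required sample size is 212 patients". Neither arm's rate is printed.
- **Other uses of these variables** (Statistical analysis): incidence is examined by sex, and McNemar's test follows questionnaire results over time. Centre and irradiation appear in no stated analysis.
- **Design**: five hospitals, sealed envelopes, no stratification stated.

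**The concern.** A Fisher test sees only the arm and one yes/no outcome per patient. Function before surgery is likely to predict function after it, and here it is measured before the operation, as part of an endpoint that refers back to it. Leaving it out of the between-arm comparison discards information already paid for. Any chance imbalance in baseline function or irradiation stays in the one estimate the trial produces, and with no stratification stated, nothing in the design limits such imbalance.

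A second, conditional worry concerns the sizing. Patients who are already dysfunctional can enter. If a case means new onset, they cannot become cases; if a case means status after surgery, they may be cases whichever ligation they had. In either situation a 20-point difference that holds among previously functional patients would be smaller over the whole arm.

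**Working it through.** **1. The article's own figures.** Exact power of the two-sided Fisher test at α = 0.05 with 100 per arm is the sum, over all pairs of case counts with p ≤ 0.05, of the product of the two binomial probabilities. At 40% vs 20% (or 80% vs 60%) this gives 0.8445, the stated value. These rates are inferred, since the article gives only the difference. The one-sided test at 0.05 gives 0.910. Dropout: 100/0.95 = 105.3, rounded up to 106 per arm, or 212. Both stated figures reproduce.

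**2. What adjustment is worth, with no dilution.** Assumptions: 100 per arm; a standard normal baseline score; a latent follow-up value correlated ρ with it; a case when the latent value crosses the cut-off giving 40% or 20%. The test is the two-sided Wald test for arm. With 8,000 simulated trials per setting (simulation error about 0.3 points):

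| ρ | Fisher, two-sided | Logistic, unadjusted | Logistic, adjusted | Gain from covariate |
|---|---|---|---|---|
| 0.3 | 84.4% | 87.6% | 89.0% | 1.4 |
| 0.5 | 84.5% | 87.7% | 92.2% | 4.5 |
| 0.6 | 84.3% | 87.2% | 94.2% | 7.1 |

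The step from Fisher to unadjusted logistic, about 3 points, is Fisher's conservatism and has nothing to do with the covariate. Under no effect (30% in both arms) the adjusted test rejected in 4.8% to 5.3% of trials and Fisher in 3.2% to 3.7%. A separate set of 5,000 trials, generated from a logistic model, agrees: with score-to-outcome correlations of 0.21, 0.37 and 0.48, power rises from 87.5%, 87.8% and 87.9% unadjusted to 88.5%, 92.3% and 95.1% adjusted.

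**3. Conditional dilution.** Let f be the share already dysfunctional before surgery (not given; assumed 10% to 30%) and suppose 40% vs 20% holds only among the rest.

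- New onset over all randomized: rate = (1 − f)·r. At f = 0.3: 28% vs 14%.
- Post-operative status, nobody recovering: rate = f + (1 − f)·r. At f = 0.3: 58% vs 44%.
- Both give a difference of (1 − f) × 20 = 18, 16 and 14 points.

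| f | New onset, two-sided (one-sided) | Status, two-sided (one-sided) | At-risk patients only, two-sided |
|---|---|---|---|
| 0% | 84.4% (91.0%) | 84.4% (91.0%) | 84.4% |
| 10% | 78.3% (86.6%) | 70.5% (80.1%) | 80.2% |
| 20% | 70.9% (81.2%) | 58.7% (69.4%) | 74.5% |
| 30% | 62.6% (74.2%) | 47.3% (58.6%) | 68.3% |

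**4. How much of that is recoverable.** Under these rules the already-dysfunctional patients carry no information about the arm, so adjusting for baseline status leaves roughly the at-risk comparison (last column, by Fisher's test). For new onset it recovers 80.2 − 78.3 = 1.9, 74.5 − 70.9 = 3.6 and 68.3 − 62.6 = 5.7 points, out of losses of about 6, 14 and 22. For status it recovers 9.7, 15.8 and 21.0 points, out of losses of about 14, 26 and 37.

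**The case against.** The strongest reply is that nothing here is wrong. If a case is new or worsened dysfunction, baseline is already inside the binary outcome and a Fisher test on it is coherent. Someone impaired before surgery can still worsen on graded scores, flow rate or residual volume, so never-a-case and always-a-case do not exhaust the possibilities. Randomization protects the test, no stratification factor is being ignored, and covariate adjustment is often left to an analysis plan, which is not shown here.

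Much of this stands, and it rules out several inferences a reader might draw:

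- **That power is certainly below the stated figure.** The article gives the 20% difference for whole cohorts of 100. If it already describes all randomized patients, or if a case means worsening, there is no dilution. The 10% to 30% prevalence is also an assumption. Under the planned one-sided test at 0.05, new-onset power at 10% prevalence is 86.6%, still above 84.45%.
- **That the unadjusted test is biased or invalid.** It is neither. Chance imbalance affects the single realised estimate and is not systematic.
- **That baseline scores and sex go unused.** They appear in other stated analyses. They are absent only from the primary comparison, and McNemar's test is within-patient and compares no arms.
- **That adjustment would restore diluted power.** It restores part of it.

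The appeal to an unseen analysis plan does not dispose of the point. The article names the primary test, so this concerns a stated choice and not an omitted detail. Even with a worsening definition, baseline level can still predict the outcome.

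**Conclusion.** The point holds as a matter of efficiency. The stated primary test is valid but takes no account of baseline function, sex, irradiation or centre as covariates. At 40% vs 20%, with a baseline correlation of 0.3 to 0.6, adjusting for a baseline score is worth about 1 to 7 points of power over unadjusted logistic regression, and leaving Fisher's conservatism about 3 more. A weakly prognostic baseline measure puts the gain at the low end. These rates and correlations are assumptions; the article gives neither.

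The dilution figures (78% to 63% for new onset, 71% to 47% for post-operative status, two-sided) apply only if the 20 points refer to patients functional at baseline, 10% to 30% are already dysfunctional, and a case is defined in one of those two ways. The article does not settle this. It is a good improvement to make and does not invalidate the design. The figures are two-sided because the sizing is; the mismatch with the one-sided analysis is a separate matter.

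**What to change.** Make the primary analysis a logistic regression of post-operative dysfunction on arm, adjusted for:

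- baseline dysfunction status, classified by the same criteria as the outcome so that it applies to both sexes, or a sex-standardised baseline score (the erectile and female indices are sex-specific, so no raw score is common to all patients);
- sex and pre-operative irradiation;
- centre, if event counts allow. At 40% vs 20% about 40 + 20 = 60 cases are expected in 200 patients. Arm, baseline, sex and irradiation use four parameters and five centres add four more, leaving 60/8 = 7.5 cases per parameter.

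Report the marginal risk difference (standardised over the trial population) with a two-sided 95% CI, and keep the two-sided Fisher test as an unadjusted sensitivity analysis.

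State the case definition alongside. If it is new onset only, baseline status would separate the outcome perfectly, so analyse the patients at risk at baseline (a subset fixed before randomization) or use a penalised fit.

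**Cost:** analysis wording only. Baseline function is already collected, and sex, irradiation and centre are known before surgery. Trial status says recruitment has not opened, so the change can be made before any outcome exists. The downside is a model-based estimate in place of a 2x2 table.

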### Participating centers and

Five non-academic public Italian hospitals will enroll patients.

### Study population

The study population consists of patients with cancer of the lower two-thirds of the rectum, who are eligible for laparoscopic low rectal resection with total mesorectal excision.

Inclusion criteria are middle or low rectal cancer (from 0 to 12 cm from the dental line), an American Society of Anesthesiologists score of I, II, or III, and a body mass index less than 30. The study will include both preoperatively irradiated and non-irradiated patients.

Exclusion criteria are prior surgery on the abdominal aorta and proven arteriosclerosis of the inferior mesenteric artery and its branches.

The study will include both pre operatively irradiated and non-irradiated patients.

Exclusion criteria: prior surgery on the abdominal aorta, proven arterosclerosis of IMA and IMA branches.

### Ethical considerations

This study is conducted in accordance with the principles of the Declaration of Helsinki and “good clinical practice” guidelines. The study was approved by a Central Ethics Committee (list of names of the Ethical Body in Additional file 1). Prior to randomization written informed consent will be obtained from all patients.

### Preoperative evaluation

Patients with a preoperative diagnosis of adenocarcinoma of the middle or lower rectum and who satisfy the inclusion criteria will be asked to participate in the HIGHLOW trial. Once informed consent is obtained, investigations will include questionnaires for the International Index of Erectile Function [27], International Consultation on Incontinence Questionnaire [28], International Prostatic Symptoms Score, Female Sexual Function Inde [29] Uroflowmetry and ultrasound measurement of post-void bladder volume will be performed pre-operatively for all patients.

### Surgery

The following steps are required in all cases, independently of randomization.

#### Laparoscopic anterior rectal resection with total mesorectal excision (without pelvic cylindrical excixion)

The first step consist in the opening of the left part of the gastrocolic ligament and the division of the left part of transverse mesocolon. The splenocolic and phrenocolic attachments are then divided, achieving complete dissection of the left colonic angle. The pelvic peritoneum is opened below the sacral promontory and the hypogastric nerves are identified and preserved. The common iliac veins, the genitofemoral nerve, the gonadic vessels, and the left ureter are successively identified and preserved.

#### For high ligation

The opening of the peritoneum proceeds cephalad, towards the duodenojejunal angle of Treitz, and the mesenteric root is incised 1 cm below the inferior margin of the pancreas. The aortomesenteric window is opened wide and the inferior mesenteric vessels are exposed. The inferior mesenteric artery is ligated and divided at 2 cm from its origin. The inferior mesenteric vein is ligated and divided below the pancreatic margin

#### For low ligation

The opening of the peritoneum proceeds upward and then laterally towards the sigmoid colon. The leftcolic artery is identified and preserved while low ligation of the inferior mesenteric artery (the superior hemorrhoidal artery) is performed. Lymphadenectomy is performed medially along the inferior mesenteric artery as far as 2 cm from the aorta.

For both groups, dissection is then continued windowing Toldt’s and Gerota’s fascias up to the parietocolic gutter. Intra-pelvic dissection is carried out through standardized planes. Dissection of the rectum starts by incision of the peritoneal fold in the pelvis. Mesorectal excision starts posteriorly by dissection through Heald’s “holy plane”, it carries on towards the lateral region of the rectum, sparing the lateral part of the lateral rectal ligaments, and extends on the anterior side in front of Denonvilliers’ fascia.

### Post-operative evaluation

Colonoscopy will be performed 30 days after surgery to evaluate anastomosis (leakage, signs of ischemia) [26]. Accurate description and pictures of the anastomosis will be produced. Questionnaires for the Internation Index of Erectile Function [27], International Consultation on Incontinence Questionnaire [28], International Prostatic Symptoms Score, and Female Sexual Function Index [29] will be administrated, and uroflowmetry and ultrasound measurement of post-void bladder volume will be performed 1 and 9 months post-operatively. Retrieved lymph nodes will be collected from the histopathological examination, and the number of positive lymph nodes on the root of the inferior mesenteric artery, the total number of lymph nodes on the mesorectum, and the number of positive lymph nodes on the mesorectum will be recorded Oncological follow up will be carried out for 5 years, according to National Comprehensive Cancer Network Guidelines [30] Version 1.2015 Rectal Cancer/Surveillance (www.nccn.org).

### Sample size calculation

A two tail Fischer exact test applied to two cohorts of 100 patients each will have 84.45 power in estimating a 20% difference in the incidence of genitor-urinary dysfunctions. With a group size of 100 patients per arm it is possible to find a significant difference (α= 0.05, β= 0.1555).

With a drop-out estimated rate of 5%, the required sample size is 212 patients. If the number of drop-outs exceed 5%, we plan to ask the ethics committee to enroll more patients to be able to keep the power of analysis well above 80%.

### Statistical analysis

The Primary end-point measure will be evaluated using Fisher’s exact test (one-sided). The different incidences of genitor-urinary dysfunction according to sex and the results of each questionnaire will be evaluated using the Mann–Whitney *U test* and the *t-*test. Mc Nemar’s test will be used to evaluate changes in questionnaires results overtime. Statistical analysis will be performed in accordance with the intention-to-treat principle.

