## Discussion

The discussion of the benefits or disadvantages between high tie and low tie in rectal surgery continues to be debated. Retrospective evaluations [9,31] have not produced a high level of significance regarding this issue. On the one hand, the risk of poor blood supply of the anastomosis could outweigh the oncological benefits of performing high ligation of the inferior mesenteric artery routinely, on the other hand a more powerful disease staging achieved with high ligation of the inferior mesenteric artery is found to be associated with an acceptable anastomotic leak rate. There is an increased risk of poor colonic stump blood supply when relying on the marginal artery alone, therefore, if this artery is not adequate, a more extended intestinal resection has to be performed, even if it is oncologically unnecessary. Performing lymphadenectomy extending to the origin of the inferior mesenteric artery even for low ligation provides data on the disease involvement of apical nodes. A significantly lower incidence of anastomotic leak in one or other group could indicate a technical policy for patients for which the vascular component might play a key role. Reduction of fistula in laparoscopic anterior rectal resection will produce a significant improvement in quality of life for these patients. Investigating pre and post-operatibegenitor-urinary function will provide a more complete assessment of the impact of laparoscopic anterior rectal resection on functional outcomes. Arterial ligation far from the hypogastric plexus could help in preserving pelvic autonomic functions, giving a better quality of life to patients.

We expect the low tie group to present a lower rate of genito-urinary function depression and post-operative fistula because of the better blood supply provided and better nerve sparing achieved.cpr

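### The primary endpoint is to be tested one-sided, but the sample size and stated power rest on a two-tailed test

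*Protocol article*

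**What the plan says.** The Sample size calculation section of the protocol article bases the trial on a two-tailed test: "A two tail Fischer exact test applied to two cohorts of 100 patients each will have 84.45 power". The target is a 20% difference in genito-urinary dysfunction, and the error rates follow: "it is possible to find a significant difference (α= 0.05, β= 0.1555". The abstract repeats the power, α and β. With 5% drop-out the total is 212.

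The next section, Statistical analysis, says of the same endpoint: "The Primary end-point measure will be evaluated using Fisher’s exact test (one-sided". It gives no significance level, no direction and no reason for moving from two tails to one.

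The only directional statement on this endpoint is an expectation in the Discussion: "We expect the low tie group to present a lower rate of genito-urinary function depression". The Discussion also opens by presenting high versus low tie as unresolved, and the stated aim is a comparison without a directional hypothesis.

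**The concern.** These are two positive statements about one test, in adjacent sections, and they disagree. This is not a detail left to an analysis plan.

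Three things are at stake.

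- **Power.** If the one-sided test is run at 0.05, the stated power and β belong to a different test.
- **Error in the favoured direction.** Moving the whole 0.05 into one tail doubles the nominal allowance there from 0.025 to 0.05.
- **The other direction.** A one-sided test cannot support a conclusion against its alternative. If it is aimed at a benefit of low ligation, a trial in which low ligation did clearly worse could only be reported as not significant.

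A result near the boundary could be called positive or negative depending on which section is followed.

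**Working it through.** **Inputs from the protocol article:** 100 per arm; 20-point difference; α = 0.05; β = 0.1555 (power 84.45%); two-tailed Fisher test for sizing; one-sided Fisher test for analysis; 5% drop-out; total 212.

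**Assumptions, because the article is silent:**
- Event rates of 40% versus 20%. The mirror image, 80% versus 60%, gives identical power. Other pairs 20 points apart were also run.
- The one-sided test uses 0.05, the only α given.
- The one-sided alternative is that low ligation is better, taken from the Discussion.

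**Method.** Exact unconditional power by full enumeration:

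Power = Σₓ Σᵧ Bin(x; 100, p₁) · Bin(y; 100, p₂) · 1{Fisher p(x, y) ≤ α}

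**Step 1: reproduce the stated power, then change the test.** Selected pairs:

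| Rates | Two-sided 0.05 | One-sided 0.05 | One-sided 0.025 |
|---|---|---|---|
| 30% vs 10% | 93.46% | 96.68% | 93.46% |
| 40% vs 20% | **84.45%** | **90.98%** | 84.45% |
| 50% vs 30% | 79.24% | 86.65% | 79.24% |
| 60% vs 40% | 78.68% | 86.03% | 78.68% |
| 80% vs 60% | 84.45% | 90.98% | 84.45% |

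The stated figure is reproduced to four digits by the two-sided test at 0.05 and, equivalently, by a one-sided test at 0.025. At 40% versus 20% the one-sided 0.05 test differs by 90.98 − 84.45 = 6.53 points, so its β is about 0.090, not 0.1555. Its lowest power over all the 20-point pairs run is 86.03%, so none of them gives 84.45%.

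**Step 2: actual error in the favoured direction**, with equal rates in both arms. The middle column is one tail of the two-sided test.

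| Common rate | Two-sided 0.05, favoured tail | One-sided 0.05 |
|---|---|---|
| 20% | 1.64% | 3.50% |
| 30% | 1.74% | 3.69% |
| 40% | 1.81% | 3.58% |
| 50% | 2.00% | 3.84% |

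The ratio runs from 3.84/2.00 = 1.9 to 3.50/1.64 = 2.1.

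**Step 3: can the choice change the conclusion?** With 20/100 events under low ligation:

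| Events, high ligation | One-sided p | Two-sided p |
|---|---|---|
| 31/100 | 0.052 | 0.104 |
| 32/100 | 0.038 | 0.076 |
| 33/100 | 0.027 | 0.054 |
| 34/100 | 0.019 | 0.038 |

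At 32 or 33 events the two sections give opposite answers.

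**Step 4: low ligation truly worse** (40% versus 20% under high ligation). A one-sided test for benefit of low ligation rejects with probability about 4 × 10⁻⁷. The two-sided test rejects with probability 84.45%.

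**Step 5: total.** 200/0.95 = 210.5, so 211, or 212 as an even total. The stated total is consistent with 100 evaluable patients per arm under the two-sided design.

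**The case against.** The strongest reply is that much of the consequence is inferred. The Statistical analysis section names no α. If one-sided 0.025 was intended, the power is exactly 84.45% and the error in the favoured direction matches that tail of the two-sided test. The direction comes only from an expectation in the Discussion, and the 40% and 20% rates appear nowhere.

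Total type I error also barely moves: at a common rate of 20% it is 3.3% two-sided and 3.5% one-sided, and every one-sided value computed is below 5%. The trial gains power rather than losing it. For genito-urinary function the article's rationale, nerve injury near the hypogastric plexus, points one way, so a one-sided hypothesis is not baseless; the debate in the Discussion turns largely on blood supply, leakage and staging.

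Most of this stands as qualification. The power and error figures depend on reading the one-sided test at 0.05, and overall error does not exceed its nominal level. The contradiction remains. The 0.025 reading is stated nowhere, and even under it one direction could not be declared. If the test pointed the other way, that would be harm from high ligation. For every pair of rates where power is not already essentially 100%, one-sided 0.05 power exceeds two-sided power, so the mismatch does not hinge on 40% versus 20%. An expected direction also does not make the opposite finding unimportant when both techniques are in wide use.

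**Conclusion.** The concern holds and should be settled before the trial starts. That the two sections contradict each other on sidedness needs no assumption.

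Reading the one-sided test at 0.05 and assuming 40% versus 20%, its power is 90.98%, not the stated 84.45%. With a benefit of low ligation as the alternative, the false-positive rate in that direction roughly doubles, and true harm of 20 points would essentially never be declared. Results such as 32 or 33 against 20 events per 100 would be positive under one section and negative under the other.

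The trial is not underpowered and its total type I error is hardly changed. The damage is to error control in the favoured direction, to the ability to conclude in the other, and to the clarity of the primary result.

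**What to change.** In the Statistical analysis section, specify Fisher's exact test as two-sided at α = 0.05 for the primary endpoint. It is also useful, though incidental to the contradiction, to report the risk difference with a two-sided 95% confidence interval. State the two event rates behind the 20-point difference, since 84.45% applies to 40% versus 20% (or 80% versus 60%) and not to every such pair.

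The cost is a small edit to the text. The stated power, 100 per arm and the total of 212 already rest on the two-sided test, so no patients are added. The Trial status section says recruitment has not opened, so the change can be made before any outcome data exist.
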